### 4.2. Baseline Characteristics Measurement

The baseline characteristics of pregnant women will be measured through the self-designed demographic and pregnancy-related questionnaires, including gestational age, occupation, education level, income, residence place, previous history of disease, gestational weeks, fetal number, existing pregnancy complications, previous pregnancy comorbidities, history of smoking, alcohol abuse and drug abuse, and information about special diet.

### 4.3. Assessment of Compliance with Dietary Recommendations

The self-management behaviors of dietary control will be assessed by a questionnaire designed by researchers based on literature review and dietary recommendations, which includes the following questions: “How many days a week do you eat according to the principle of “breakfast, lunch, and dinner, and 2–4 extra meals?”; “How many days a week do you match the staple food according to the principle that the ratio of coarse grain to fine grain is 1:2 or 1:4?”; “How many days a week do you subtract the corresponding staple food when eating starchy foods (for example, 100 g of potatoes can be exchanged with 25 g of rice, millet, and sorghum rice)?”; “How many days a week do you follow the food exchange strategy as recommended by the medical staff?”; “How many days a week do you refer to the GL value of food when choosing foods?” Each item is scored according to the number of days in which behaviors occurred, with 0 to 7 points assigned from 0 to 7 days. The total score ranges from 0 to 35 points. 0–11 points, 12–23 points, and 24–35 points indicate low, medium, and high levels of dietary self-management behavior, respectively.

The self-efficacy of participants will be assessed by the Chinese version of the Diabetes Management Self-Efficacy Scale (C-DMSES). The DMSES was originally developed by van der Bijl et al. [33]. Wu et al. have translated it into Chinese version [34]. In this study, we will use the nutrition-related subscale of C-DMSES to assess the self-efficacy of dietary control in women with GDM. The nutrition-related subscale has nine items, and each is rated on a 5-point scale (1 = “strongly disagree” 5 = “strongly agree”) [34]. Higher scores indicate better self-efficacy. The Cronbach’s alpha of the nutrition-related subscale of C-DMSES is 0.93 [34].

Maternal dietary intake will be recorded through the 24-h dietary recalls questionnaire. Participants will be asked to record dietary information for two business days and one holiday in one week and record the types and amounts of food intake, including main meals, extra meals, and snacks. In addition, the average daily GL value will be taken as the mean of the total GL value of all food exchange servings included in the dietary records. Food exchange servings are converted from the total energy of food consumed.

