The traditional food exchange serving (FES) is a classic meal planning of MNT [12], which is designed according to dietary recommendations. By following the traditional FES, women with GDM can control daily caloric intake and the proportion of three thermogenic nutrients to just enough to meet the needs for healthy pregnancy [12]. Currently, the traditional FES has been widely used in dietary intervention for diabetic patients in East Asian countries [13,14,15], and its effectiveness has been proven [13,16]. However, despite such advantages of the traditional FES, it cannot distinguish differences in glycemic response caused by various foods within the same food type [13]. This leads to the possibility that people with diabetes may still choose foods that have a relatively large impact on blood glucose, although following the traditional FES. Therefore, FES based on glycemic load (GL) was put forward as a new meal planning of MNT [17].

GL was proposed by Salmeron et al. in 1997, which is used to reflect the increasing potential of insulin demand caused by carbohydrates in foods [18]. In 2006, according to dietary habits of Chinese people, Sun et al. developed the new food exchange system based on GL [17]. Different from the traditional FES, FES based on GL suggests that people with diabetes should refer to GL value of each food before selecting foods in the last step of the traditional FES [17]. Existing evidence shows that following FES based on GL could help women with GDM to achieve better results in controlling blood glucose compared to following the traditional FES [19,20]. A meta-analysis of 29 studies also showed that ethnic Chinese women with GDM can benefit from choosing foods with low GL value to improve glucose metabolism and reduce the risks of adverse pregnancy outcomes [21].

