## 2. Research Hypothesis

We hypothesize that after the intervention, women with GDM who receive the intervention program designed based on BCW will have (1) higher scores of self-management behavior and self-efficacy, (2) better results of maternal glucose metabolism, and (3) lower incidences of common adverse pregnancy outcomes than women with GDM who receive general dietary management.

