## 4. Measures

Primary outcomes for compliance with dietary recommendations include self-management behaviors and self-efficacy of dietary control, and the average daily GL value. Secondary outcomes for maternal glucose metabolism include results of OGTT, FBG, 2 h PBG, and HbA1c. Secondary outcomes for adverse pregnancy outcomes include non-normal gestational weight gain (GWG) (excessive GWG or insufficient GWG), insulin use during pregnancy, cesarean section, premature delivery, macrosomia, and fetal intrauterine growth restriction. The timeliness of data collection is shown in Table 2.

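### Item 3 of the self-management questionnaire applies only on starchy-food days but is scored as a raw day count, so up to 7 of the 35 points of a primary outcome reflect food choice and not compliance

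*Protocol article*

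**What the plan says.** Section 4 (Measures) gives the score its status: "Primary outcomes for compliance with dietary recommendations include self-management behaviors and self-efficacy of dietary control, and the average daily GL value". Section 2 states the expected direction, with the intervention arm predicted to have "higher scores of self-management behavior and self-efficacy".

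Section 4.3 describes a five-item questionnaire written by the researchers. Four items concern the meal pattern, the mix of coarse and fine grain, use of the recommended exchange strategy, and consulting GL values. The third asks: "How many days a week do you subtract the corresponding staple food when eating starchy foods". One rule covers all five: "Each item is scored according to the number of days in which behaviors occurred, with 0 to 7 points assigned from 0 to 7 days". Summed over the items, this gives: "The total score ranges from 0 to 35 points". The bands are: "0–11 points, 12–23 points, and 24–35 points indicate low, medium, and high levels of dietary self-management behavior, respectively".

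Table 2 marks this score at 37 weeks of gestation only. The Discussion (Section 7) lists as a limitation that one questionnaire has not been validated. It does not mention the scoring of item 3.

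**The concern.** The other four items describe things a woman can do on any day of the week. Item 3 is conditional, because subtraction can happen only on a day when a starchy food is eaten. The scoring rule ignores the condition, so the item measures the number of starchy-food days multiplied by the share of those days on which she subtracted. A woman who ate none in the week, and so broke no rule, gets the same 0 as a woman who ate them daily and never subtracted.

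Starchy-food days are also determined after randomization. Average daily GL is itself a primary outcome, so the trial is looking for a difference in food choice between arms. If starchy-food days differed by arm, part of the difference in the self-management score would reflect that and not compliance. If they did not differ, their variation between women would still add spread to a comparison with 30 per group. Section 3.5 says that the pilot results will set the size of the future study, and Section 6 plans Cohen's d, so any distortion could carry forward.

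**Working it through.** **Inputs.** Five items of 0 to 7 points, the 0 to 35 range and the three bands come from Section 4.3. The number of starchy-food days per week, d, is not given, so it is run over its full range of 0 to 7. Let k be the number of days on which staple food was subtracted (k ≤ d).

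**1. Reproduce the stated range.** 5 × 7 = 35, as stated. Each band holds 12 values. The scoring is therefore fully specified in the article, and no adjustment for item 3 is hidden in the total.

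**2. Ceiling for a fully compliant woman.** Four items give 4 × 7 = 28. Item 3 gives k = d. Maximum total = 28 + d.

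| d | Item 3 | Maximum total |
|---|---|---|
| 0 | 0 | 28 |
| 1 | 1 | 29 |
| 3 | 3 | 31 |
| 4 | 4 | 32 |
| 7 | 7 | 35 |

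The range caused by d alone is 7 of 35 points, or 20%.

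**3. Effect on the bands.** Take the other four items at 5 days each (4 × 5 = 20) and full compliance on item 3, so that the total is 20 + d.

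| d | Total | Band |
|---|---|---|
| 0 | 20 | medium |
| 3 | 23 | medium |
| 4 | 24 | high |
| 7 | 27 | high |

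The band changes although compliance is the same in every row.

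**4. Ordering within item 3.** Subtracting on 6 of 7 starchy-food days (86%) scores 6. Subtracting on 1 of 1 (100%) scores 1. The more compliant woman scores 5 points lower on this item.

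**5. Effect on the arm comparison.** If both arms subtract on the same share p of starchy-food days, the spurious difference in mean score is p × (mean d in one arm − mean d in the other). At p = 1, a gap of one day gives 1 point and a gap of two days gives 2 points. The article gives no standard deviation for the total. Over an assumed range of 4, 6 and 8 points, 1 point is 0.25, 0.17 and 0.125 SD, and 2 points is 0.50, 0.33 and 0.25 SD. With a gap of zero there is no bias, only added variance.

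**6. Scores under the fix.** With item 3 = 7 × k/d, the two women in step 4 score 7 × 6/7 = 6 and 7 × 1/1 = 7, which is the right order. A fully compliant woman scores 28 + 7 = 35 for any d ≥ 1, and 28 × 35/28 = 35 at d = 0. The woman in step 3 scores 20 × 35/28 = 25 at d = 0 and 20 + 7 = 27 at any d ≥ 1, in the high band throughout.

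**The case against.** Four points on the other side deserve weight.

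- **The effect is confined to one item.** A reader might infer that a compliant woman who eats few starchy foods scores near zero, or that the 12 and 24 cut-offs are out of her reach. Neither holds. The low score is on item 3 only. With the other four items at 7 she totals at least 28, inside the high band. Section 6 also names no analysis of the bands.
- **The total is not shown to fall as compliance rises.** A reader might infer this from step 4. Suppose, on assumed values, that controls eat starchy foods on 4 days and subtract on 50% (4 × 0.5 = 2.0), while intervention women eat them on 2 days and subtract on 90% (2 × 0.9 = 1.8). Item 3 drops by 0.2 points. The total would fall only if the other four items together gained less than 0.2 of their 28 points. The documents do not support such a forecast. With the score marked only at 37 weeks, no change within a woman would be seen either.
- **Both arms are taught the same exchange system.** Sections 3.8 to 3.8.2 give GL-based materials and instruction to everyone, and no text tells women to avoid starchy foods. An arm difference in d could arise only indirectly, for instance through stronger uptake in the arm that also gets the food atlas, scales and weekly help with recipes. That is possible, but not shown.
- **The study is a pilot and admits an unvalidated questionnaire.** This limits the consequence. It does not identify or repair the scoring rule.

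It might also be said that women will answer by habit and give 7 even if they seldom eat starchy foods. The stated rule counts days on which the behaviour occurred. If some women answer 0 and others 7 for the same conduct, that is a measurement fault of its own.

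**Conclusion.** The point stands as a scoring defect in one item of a primary outcome. Under the stated rule, up to 7 of 35 points depend on how often starchy foods are eaten, and a woman who never breaks the item 3 rule can be placed in a different band for that reason alone. This follows from the item wording and the scoring rule and needs no outside assumption.

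The effect on the treatment comparison is less certain. Added noise is expected wherever d varies between women. Bias requires d to differ between arms. The article gives no intake frequency, so neither the size nor the direction of any bias can be stated, and the SD-based figures above are illustrations. The change is worth making because it is cheap and the score is a primary outcome, not because a wrong trial result has been demonstrated.

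**What to change.** Before data collection:

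1. Add one question: on how many days in the week were starchy foods eaten?
2. Score item 3 as 7 × (days subtracted / days eaten).
3. When days eaten is 0, treat item 3 as not applicable and prorate the total as the four-item sum × 35/28.
4. State a rounding rule, because totals will no longer always be whole numbers and the bands are written in whole points. For example, 19 × 35/28 = 23.75 falls between the medium and high bands.
5. Report the number of starchy-food days by arm.
6. Report the four-item total (0 to 28), without item 3, as a sensitivity analysis.

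The cost is one question and a revised scoring paragraph. The questionnaire was written for this study and is unvalidated, so no established scoring is broken. The downside is that the ratio is coarse when starchy foods are eaten on only 1 or 2 days: on a single such day the item is either 0 or 7. Step 6 shows whether the conclusion depends on this. If data have already been collected without the extra question, the four-item total can still be computed from them.

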### 4.4. Maternal Glucose Metabolism Measurement

The laboratory department of the hospital will be responsible for measuring the experimental indicators related to maternal glucose metabolism. The experimental indicators include OGTT, FBG, 2 h PBG, and HbA1c, which will be measured at the study entrance and again at 37 weeks of gestation. Data on the results of these experimental indicators will be collected from the prenatal and delivery records of participants.

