### 3.2. Research Setting and Participant Eligibility Criteria

The study will be conducted in the obstetric clinic of a Grade 3A hospital in Wuhan, Hubei Province. Pregnant women diagnosed with GDM by a clinical 75 g oral glucose tolerance test (OGTT) at 24 weeks of gestation are eligible to participate. The glucose concentration thresholds of pregnant women accord with IADPSG criteria in 2010 [28]: Fasting blood glucose (FBG) ≥ 5.1 mmol/L and/or 1-h plasma glucose after taking sugar ≥ 10.0 mmol/L and/or 2-h plasma glucose after taking sugar ≥ 8.5 mmol/L. Furthermore, women with GDM who are eligible must meet the following inclusion criteria: (1) Aged between 18 and 40 years, (2) natural pregnancy, (3) singleton pregnancy verified by ultrasound, (4) have adequate cognitive and behavioral abilities, (5) no previous endocrine-related diseases, such as hyperthyroidism, hypothyroidism, and Cushing’s syndrome, (6) voluntarily participate in this study and sign the informed consent form.

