#### 3.8.2. Intervention Group

Pregnant women in the intervention group will receive dietary intervention designed based on BCW, including an individual primary consultation at enrollment, two additional consultations at reviews, and online consultations. Each essential condition in COM-B system often corresponds to multiple intervention functions, policies, and behavioral change techniques (BCTs). Therefore, researchers will select intervention components according to APEASE criteria (affordable, practical, efficacious, acceptable, safe, and equitable) in this study [25]. The matrix of links between the components of BCW (COM-B system, intervention functions, and policy category) for the intervention is described in Table 1.

In the individual primary consultation at enrollment, four intervention strategies will be implemented: (1) Determining the positive and adverse aspects of pregnant women’s current dietary behaviors, and emphasizing the benefits of positive behaviors and the consequences of adverse behaviors, (2) clarifying the importance and principles of dietary control for the treatment of GDM and helping pregnant women to set goals for glycemic control, (3) providing the same guidance materials and explaining the content of the paper guidance materials as the control group for designing daily recipes, showing the additional food atlas showing the shape, volume ration and energy value of food under different grams, different dry and wet states and different cooking methods, and providing the same type of simple food scales to pregnant women for determining the amount of food intake, training pregnant women to design the daily recipes.

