In the online consultation at three days after enrollment, three intervention strategies will be implemented: (1) Evaluating the dietary behaviors of pregnant women in the past three days and correcting the wrong dietary behaviors as the control group, (2) informing pregnant women’s main caregivers about the importance of dietary control for women with GDM and the benefits of providing good family support, i.e., enhance pregnant women’s motivation to comply with dietary control, (3) putting forward some suggestions on how to control the diet when participating in a multi-person dinner. For example, use a spoon to estimate the intake amount of a certain food. In the online consultation at 7:00 pm every Friday, two intervention strategies will be implemented: (1) Providing the same online guidance team to answer pregnant women’s questions and conduct health education in the WeChat communication group as the control group, (2) helping pregnant women to design recipes for the next week’s diet.

In the first additional consultation in one week after enrollment, two intervention strategies will be implemented: (1) Deciding the next phase of treatment for pregnant women according to the reexamination results of maternal glucose metabolism, just as researchers do for the control group, (2) setting up the collaborative dietary management group of three women with GDM and encourage them to share dietary control experience, so as to achieve peer education and model setting.

In the second additional consultation at 28 weeks of gestation, researchers will instruct pregnant women to increase 450 kcal on their daily basal energy requirements calculated from their pre-pregnancy BMI and body energy coefficient [32], so as to properly adjust exchange servings of a certain food.

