The first additional consultation at review	At one week after enrollment	Pregnant women	Communication; Guideline; Service provision;	*Persuasion, incentivization, and enablement*: Re-measure blood glucose, and look back and analyze the dietary-related reasons for the positive or reverse results of controlling blood glucose	√	√	√	√	√	√
			Communication;	*Education, persuasion, and modeling*: Set up the three-person cooperation group to achieve peer education		√	√		√	√
The second additional consultation at review	At 28 weeks of gestation	Pregnant women	Communication;	*Education*: Recalculate total daily energy requirements, and adjust exchange servings of a certain food for meeting the need for the healthy pregnancy		√			√	

**Table 2 ijerph-19-10726-t002:** Timeliness of Data Collection.

	Enrollment	A Week after Enrollment	28 Weeks of Gestation	37 Weeks of Gestation	After Intervention (Before Delivery)	After Delivery

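### Section 4.4 and Table 2 give different measurement times for all four glucose indicators; under Table 2 the first HbA1c and 2 h PBG follow the start of the intervention, and OGTT has no follow-up value

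*Protocol article*

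**What the plan says.** Section 4 lists the glucose outcomes: "Secondary outcomes for maternal glucose metabolism include results of OGTT, FBG, 2 h PBG, and HbA1c". Section 4.4 gives the times for all four together: "which will be measured at the study entrance and again at 37 weeks of gestation".

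Table 2 gives other times. The 75 g OGTT has one tick, at enrollment. FBG, 2 h PBG and HbA1c each have two ticks, one under "A Week after Enrollment" and one at 37 weeks, and none at enrollment.

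The intervention begins before the one-week point. Section 3.8.2 states: "In the individual primary consultation at enrollment, four intervention strategies will be implemented". It then continues: "In the online consultation at three days after enrollment, three intervention strategies will be implemented". The one-week review decides the next phase "according to the reexamination results of maternal glucose metabolism", which presupposes an earlier value.

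Section 3.2 requires that women be "diagnosed with GDM by a clinical 75 g oral glucose tolerance test (OGTT) at 24 weeks of gestation", with fasting, 1-h and 2-h thresholds. Section 3.6 recruits them when they return for that result. Section 6 plans a repeated measures MANOVA with post-hoc pairwise comparisons.

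**The concern.** The two schedules disagree on every glucose indicator, so whoever collects the data must choose one. The choice affects the second hypothesis in Section 2, better maternal glucose metabolism.

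If Table 2 is followed, FBG, 2 h PBG and HbA1c each have exactly two scheduled values, and both fall after randomisation. The group-by-time term of a repeated measures analysis is then the difference between arms in change from one week to 37 weeks. Any separation of the arms already present at one week is subtracted from it. An entry value that was not taken cannot be obtained later.

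OGTT raises a separate problem. A test done only at enrollment describes who entered the trial and cannot show an effect of treatment, yet Section 4 lists it as a secondary outcome.

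Section 3.5 adds to the stakes. The stated purpose of the pilot is to estimate effect size, and the future sample size is to be calculated from its results.

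**Working it through.** **Step 1: the two schedules side by side.** Each Table 2 row has six cells under six column headings, so the ticks can be placed without doubt.

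| Indicator | Section 4.4 | Table 2 | Conflict |
|---|---|---|---|
| OGTT | entrance, 37 weeks | enrollment | second time point |
| FBG | entrance, 37 weeks | one week, 37 weeks | first time point |
| 2 h PBG | entrance, 37 weeks | one week, 37 weeks | first time point |
| HbA1c | entrance, 37 weeks | one week, 37 weeks | first time point |

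**Step 2: what differs between the arms before one week (Sections 3.8.1 and 3.8.2).**
- Enrollment, intervention arm only: glycemic goal setting, food atlas, food scales, training in recipe design.
- Day 3, intervention arm only: session for the main caregiver, advice on shared meals.
- Both arms: guidebook, exchange table, explanation of how to design recipes, correction of dietary behavior on day 3.

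**Step 3: what pre-randomisation glucose data Table 2 still provides.** The enrollment OGTT gives a fasting value and a 2-h value after a glucose load. The first can serve as a fasting baseline. The second is not a postprandial value, though it may be prognostic for one. No entry HbA1c is scheduled.

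**Step 4: effect on each analysis.** Let d be the true difference at 37 weeks in SD units, f the fraction of it present at one week, and r the correlation between the two measurements, with equal SDs.
- Comparison at 37 weeks only: expected effect d, whatever f is.
- Change from one week: expected effect d(1 − f), SD of change √(2(1 − r)).
- Adjustment for the one-week value: expected effect d(1 − rf).

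**Step 5: illustration.** The protocol states no effect size, SD or power, so there is no figure of its own to reproduce. From the documents: 30 per arm and a 0.05 level. Assumed: two-sided test, d = 0.74 (close to the 0.736 that gives 80% power in a two-sample t test with 30 per arm), r and f.

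With r = 0.5 the SD of change is √(2 × 0.5) = 1. The non-centrality is the standardised effect × √(30/2) = effect × 3.873, against a critical value of 2.00 on 58 degrees of freedom.

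| f | Change-score effect | Non-centrality | Power |
|---|---|---|---|
| 0 | 0.74 | 2.87 | about 80% |
| 0.10 | 0.67 | 2.58 | about 72% |
| 0.25 | 0.56 | 2.15 | about 56% |
| 0.50 | 0.37 | 1.43 | about 29% |

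A normal approximation gives one to two points more (for example 30% at f = 0.50).

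At f = 0.50 with other correlations:
- r = 0.3: SD of change √1.4 = 1.183, standardised effect 0.37/1.183 = 0.313, power about 22%.
- r = 0.7: SD of change √0.6 = 0.775, standardised effect 0.37/0.775 = 0.478, power about 44%.

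Adjusting for the one-week value at r = 0.5 and f = 0.50 gives 0.74 × (1 − 0.25) = 0.555 SD, still below 0.74. The 37-week comparison keeps 0.74 SD and about 80% power.

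**The case against.** The strongest reply is that this is an inconsistency between text and table on secondary outcomes of a pilot, and that little bias follows from it. Several parts of that reply stand.

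- A reader might infer that the protocol uses the one-week value as its baseline. It never says so. Section 4.4 speaks of study entrance, and the one-week FBG and 2 h PBG have a purpose of their own at the review. The value would become the reference only because it is the first one scheduled.
- A reader might infer that no pre-randomisation glucose value exists under Table 2. The enrollment OGTT supplies a fasting value. The strict gap is HbA1c and 2 h PBG.
- A reader might infer that the second hypothesis is necessarily biased toward zero. Section 2 predicts a difference between groups after the intervention, and a comparison at 37 weeks is untouched by the one-week value. The reduction arises for a group-by-time or change contrast, or on adjustment for the one-week value.
- A reader might infer that the trial loses a known amount of power. No power was planned, the documents do not give f, and f may differ between FBG, 2 h PBG and HbA1c. The controls also receive much of the early dietary teaching, and the intervention's peer group starts only at the one-week review, so early separation could be small.

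The contradiction itself is not answered. The article prints both schedules, so condensation does not explain the difference. Section 6 does name a repeated measures analysis, and with two scheduled values its group-by-time contrast is the change from one week. OGTT remains an outcome without a follow-up tick.

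**Conclusion.** The point holds as a contradiction with a conditional consequence. Section 4.4 and Table 2 disagree on one time point for each of the four glucose indicators, and the documents do not settle which governs. If Table 2 governs, the first HbA1c and 2 h PBG, and the first FBG other than the fasting OGTT value, may already contain some treatment effect. The group-by-time contrast would then be reduced by an unknown fraction f. OGTT would have no value that could reflect treatment.

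The documents do not support a definite amount of bias. The fall from about 80% to about 30% power rests on assumed values of d, r and f, with about 22% to 44% at f = 0.5 for correlations of 0.3 to 0.7. It applies to a change score only. With f = 0, or with a plain comparison at 37 weeks, nothing is lost.

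**What to change.** Reconcile Section 4, Section 4.4 and Table 2.

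1. Place the reference FBG, 2 h PBG and HbA1c at study entrance, before the first arm-specific contact, as Section 4.4 already implies. Mark the one-week values as post-randomisation follow-up and never use them as the reference. Their use at the one-week review is unaffected.
2. If no entry values are taken, compare the arms at 37 weeks. Adjust FBG for the fasting OGTT value. Adjust 2 h PBG for the 2-h post-load value, as a prognostic covariate only. Compare HbA1c without a baseline HbA1c, with OGTT values as optional covariates.
3. Either give OGTT the 37-week measurement that Section 4.4 states, or remove it from the secondary outcomes and keep it as a covariate.

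Cost: the text and table corrections are small. Entry HbA1c and 2 h PBG may need added tests if they are not already routine, and a 37-week OGTT is a further test if it is kept as an outcome. The covariate option needs no new test, but leaves HbA1c without a baseline of its own.
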